**Figure 2 fig2:**
[figure not shown]
Comparison of the two magnetized needle types used in this study (26G × 60 mm and 25G × 100 mm).

All four participating clinical sites routinely use both types of needles in daily practice, depending on actual clinical circumstances. For the purpose of comparative analysis, two sites will be designated to contribute only cases treated with short needles, while the other two sites will contribute only cases treated with long needles. This approach represents a site-level data extraction scheme, rather than a randomized allocation process, and is designed to enable comparative analysis of procedures performed in routine clinical practice without modification of standard patient care.

The study procedures consist of three stages: screening, the treatment visit (Visit 1), and post-procedure follow-up at 24 to 36 h. After providing written informed consent, participants undergo screening, during which demographic characteristics and relevant medical history are collected, and eligibility is assessed based on predefined inclusion and exclusion criteria. Participants who meet all eligibility criteria proceed directly to Visit 1, during which the ultrasound-guided pharmacopuncture intervention and all corresponding study assessments are conducted.

During Visit 1, all enrolled participants undergo a single ultrasound-guided PDRN pharmacopuncture procedure following a standardized protocol. Prior to the intervention, baseline assessments are conducted, including Numerical Rating Scale (NRS) scores for LBP and radiating leg pain, lumbar ROM, the Oswestry Disability Index (ODI), and the Patient-reported Percentage Pain Reduction(PRPPR) score. After the baseline evaluation, the practitioner identifies the interfascial QPI space using high-resolution ultrasonography and then performs the injection using a magnetically guided needle system, administering 1–2 mL of the PDRN pharmacopuncture solution.

The procedure is performed using an in-plane needle approach, enabling real-time visualization of the needle trajectory and tip through ultrasound imaging combined with a magnetic needle-tracking system. Both groups receive the same injection technique and target the same anatomical site; however, the SNG uses a 26G × 60 mm needle, while the LNG uses a 25G × 100 mm needle. All other procedural variables remain consistent across groups.

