During the procedure, performance-related indicators are recorded, including the number of needle insertions, total procedure time, confirmation of needle-tip arrival at the deep target layer (QPI space), and visualization of the hypoechoic spread during injectate delivery. All ultrasound images and needle-tracking log data are stored for subsequent analysis.

Immediately after the procedure, pain intensity (NRS), PRPPR, and ROM are reassessed. Additionally, the operator completes a usability questionnaire to evaluate needle visibility, tracking stability, handling comfort, confidence in target engagement, perceived procedural workload, and overall satisfaction. Any immediate adverse events occurring at this time point are documented in detail.

Follow-up assessments are conducted via telephone within 24 to 36 h after the procedure. During this contact, changes in pain intensity (NRS), PRPPR, functional status in daily activities, and the presence of any delayed adverse events are evaluated. All collected data are recorded using institution-specific Case Report Forms (CRFs) and included in the final analysis after de-identification. A summary of the study procedures is presented in Table 1.

**Table 1 tab1:** Summary of study procedures and assessment timeline.

Study procedure	Period		
	Screening*	Visit 1	F/U^†^
	-1D^‡^	Baseline (0)	~1D
Explanation of the study and obtaining consent	○		
Determination of inclusion/exclusion criteria	○		
Demographic survey^a^	○		
Medical history investigation^b^	○		
ODI (Baseline)^c^		○	
NRS (Pre-/Post-intervention, Day 1)^d^		○	○
PRPPR (Post-intervention, Day 1)^e^		○	○
ROM (Range of Motion) (Pre-/Post-intervention)^f^		○	
Intervention (Short needle vs. Long needle)		○	
Adverse event assessment^g^		○	○

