*If the subject is deemed eligible after screening, the first intervention will be performed immediately after obtaining informed consent. ^†^A telephone-based follow-up will be conducted within 1 day (24–36 h) after Visit 1. ^‡^D indicates “Day.” ^a^Demographic survey: information on gender, age, year of birth, height, weight, and other baseline characteristics will be collected. ^b^Medical history: includes previous history of low back pain(LBP), hypertension, diabetes, osteoarthritis, sleep disorders, psychiatric history, current medications, smoking history, and alcohol consumption. ^c^ODI (Oswestry disability index): the ODI is a validated questionnaire assessing functional disability related to LBP. It consists of 10 items covering pain intensity and daily activities, and yields a score ranging from 0 to 100%, with higher scores indicating greater disability. In this study, ODI is administered only at baseline to evaluate initial functional status. ^d^NRS (numeric rating scale): pain intensity for LBP will be assessed on a 0–10 scale, where higher scores indicate more severe pain. ^e^PRPPR (patient-reported percentage pain reduction): subjects will be asked to report the perceived percentage of pain reduction compared with pre-intervention status, on a 0–100% scale, both immediately after treatment and at Day 1 follow-up. ^f^ROM (range of motion): lumbar ROM—including flexion, extension, lateral flexion, and rotation—will be assessed to evaluate functional changes. ^g^Adverse events: adverse events or unexpected symptoms occurring immediately after the procedure or during follow-up will be assessed and recorded.

The study protocol has been submitted for Institutional Review Board (IRB) approval. Ethical approval will be obtained prior to the initiation of participant enrollment. No participants have been recruited or exposed to the intervention at the time of manuscript submission.

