##### Patient-reported percentage pain reduction, PRPPR

2.5.2.3

PRPPR is a subjective metric in which participants rate their pre-procedure pain intensity as 100%, then report the percentage by which their pain has decreased after the procedure on a 0–100% scale. In pain intervention research, it has been suggested that evaluating the perceived percentage reduction—not just the absolute numerical change (e.g., NRS difference)—may provide a more sensitive measure of clinical improvement, especially when assessing early or immediate treatment response (20–22). Based on this rationale, PRPPR was selected as a secondary outcome measure in this study to capture the immediate analgesic effect following a single session of ultrasound-guided pharmacopuncture.

As this study is a prospective, comparative, observational trial conducted in a real-world clinical setting, complete assessor blinding based on needle type (Short vs. Long) is not feasible. Therefore, outcome assessors will evaluate participants in an unblinded state, with access to group allocation information.

Although this approach may introduce potential measurement bias, several strategies have been implemented to minimize its impact. All participating centers will adhere to a standardized assessment protocol, and outcome assessors will receive uniform training prior to the study’s initiation. Furthermore, all outcome measures—including NRS, ROM, ODI, and PRPPR—will be recorded consistently according to predefined operational definitions.

Despite these procedures, residual bias inherent in non-blinded assessments cannot be entirely eliminated. This limitation should be considered when interpreting the study findings.

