#### Statistical analysis

2.6.2

All statistical analyses will be performed using R software (version 4. X. X; R Foundation for Statistical Computing, Vienna, Austria). All tests will be two-tailed, with statistical significance defined as *p* < 0.05. Continuous variables will be summarized as mean ± standard deviation or median with Interquartile Range (IQR), depending on the data distribution. Categorical variables will be presented as frequencies and percentages.

For the primary outcome, changes in NRS scores will be analyzed according to the data distribution. Between-group comparisons will be performed using an independent *t*-test if the normality assumption is satisfied; otherwise, the Wilcoxon rank-sum test will be used. Within-group changes will be assessed using a paired *t*-test or the Wilcoxon signed-rank test, depending on whether the data meet normality assumptions.

For the secondary outcomes, changes in lumbar ROM from baseline will be analyzed using the same statistical methods applied to the primary outcome. Between-group comparisons will be conducted using an independent *t*-test or the Wilcoxon rank-sum test, while within-group comparisons will be analyzed using a paired *t*-test or the Wilcoxon signed-rank test, depending on data normality.

The ODI will be categorized into predefined functional disability levels, and differences in distribution between groups will be analyzed using the Chi-square test or Fisher’s exact test, as appropriate.

PRPPR will be assessed immediately after treatment and again at 24–36 h post-intervention. Between-group comparisons will be conducted using an independent *t*-test or the Wilcoxon rank-sum test, while within-group comparisons will be analyzed using a paired *t*-test or the Wilcoxon signed-rank test, depending on the data characteristics.

In addition, procedural characteristics and usability-related variables associated with needle length—including deep-layer reach success rate, number of insertions, procedure time, and operator usability score—will be summarized using descriptive statistics. When appropriate, exploratory between-group comparisons will be conducted using the Mann–Whitney U test or the Chi-square test. These analyses will serve as supportive reference analyses and will not directly influence the interpretation of the primary clinical outcomes.

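### PRPPR is collected on a 0–100% reduction scale that cannot record worsened pain, and section 2.1 lists it as a baseline measure against the rest of the protocol

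*Protocol article*

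**What the plan says.** **Scale.** Footnote e of Table 1 says "subjects will be asked to report the perceived percentage of pain reduction compared with pre-intervention status, on a 0–100% scale". Section 2.5.2.3 agrees: "participants rate their pre-procedure pain intensity as 100" per cent and then "report the percentage by which their pain has decreased after the procedure on a 0–100% scale". Neither place provides for an increase in pain. Section 2.5.2.3 makes PRPPR a secondary outcome.

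**Timing.** Section 2.1 (Study design) begins a list with "Prior to the intervention, baseline assessments are conducted, including Numerical Rating Scale (NRS) scores" and ends it with "the Oswestry Disability Index (ODI), and the Patient-reported Percentage Pain Reduction(PRPPR) score". It then says: "Immediately after the procedure, pain intensity (NRS), PRPPR, and ROM are reassessed". The PRPPR row of Table 1 shows post-intervention and Day 1 only, and section 2.6.2 says "PRPPR will be assessed immediately after treatment and again at 24–36 h post-intervention".

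**Related measures.** NRS is taken before and after the procedure and at Day 1, and its immediate change is the primary outcome (section 2.5.1). Section 2.9 names pain or tenderness at the insertion site and transient paresthesia as possible reactions. Adverse events are assessed immediately and again at 24–36 h.

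**The concern.** PRPPR is asked immediately after a deep needle insertion and again the next day, and the protocol itself foresees local pain. Some participants may therefore feel worse than before, and the item gives them nowhere to say so. This is fixed when the data are collected: no analysis can recover a value that the form never asked for.

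The two arms differ in needle length and gauge, so pain after the procedure is one way in which they could plausibly differ. A measure that cannot show deterioration is weak at that point, and the comparison is also unblinded and non-randomized.

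The baseline entry is a separate defect. Pre-procedure pain is 100% for everyone by definition, so a pre-procedure reduction carries no information. Listing it invites sites to collect an empty value.

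**Working it through.** **The plan's own figure.** The protocol gives no planning figure for PRPPR. Its one sample size is for NRS: d = 0.56, two-sided 5%, 80% power. The two-sample t-test gives 51.03, rounded up to 52 per group (104 in total). With 10% dropout, 104 / 0.9 = 115.6, so 116, which the target of 120 covers. The figure reproduces, and PRPPR plays no part in it.

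**Inputs for PRPPR.** The documents give no mean or SD. Assume that the true percentage change X is normal with SD s = 25 to 40 points, equal in both groups. The upper limit of 100% is not modelled, because it is a real maximum for a reduction.

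**If worsening is coded 0.** The recorded mean is E[max(0, X)] = μΦ(μ/s) + sφ(μ/s). For example, with μ = 20 and s = 25: 20 × 0.7881 + 25 × 0.2897 = 23.0.

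| True mean | Share below 0 (SD 25 / 40) | Recorded mean (SD 25 / 40) |
|---|---|---|
| 20 | 21% / 31% | 23.0 / 27.9 |
| 30 | 12% / 23% | 31.4 / 35.2 |
| 40 | 5% / 16% | 40.6 / 43.3 |
| 50 | 2% / 11% | 50.2 / 52.0 |
| 60 | 1% / 7% | 60.1 / 61.2 |

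A true 10-point difference is then recorded as follows (from unrounded means):

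| Means compared | SD 25 | SD 40 |
|---|---|---|
| 20 vs 30 | 8.4 (−16%) | 7.3 (−27%) |
| 40 vs 50 | 9.6 (−4%) | 8.7 (−13%) |
| 50 vs 60 | 9.9 (−1%) | 9.1 (−9%) |

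**If worsening is left blank.** The mean of those who answer is μ + sφ(μ/s)/Φ(μ/s). With μ = 20 and s = 25 this is 20 + 25 × 0.2897 / 0.7881 = 29.2, so the upward bias is larger than with zero-coding.

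**Unequal spread, coded 0.** The direction is no longer fixed:
- Means 30 vs 40 with SDs 20 vs 40: the difference grows from 10.0 to 12.75.
- Means 30 vs 40 with SDs 40 vs 20: it falls from 10.0 to 4.92.
- Equal means of 30 with SDs 30 vs 45: a difference of 4.3 appears where none exists.

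**Partial check from section 2.6.1.** The cited chronic LBP trial had mean reductions of 1.76 and 2.74 points with d = 0.56, which implies SD = 0.98 / 0.56 = 1.75. Under normality about 16% and 6% would fall below zero, and flooring would cut the difference from 0.98 to 0.88 (−10%). For an immediate fall of 4 points, the size cited for ultrasound-guided hydrodissection, with the same SD only about 1% would fall below zero.

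**Timing, side by side.** Section 2.1 lists PRPPR before the intervention and speaks of repeating it afterwards. Table 1, footnote e, section 2.5.2.3 and section 2.6.2 all place it only after treatment and at Day 1. Footnote e is right on timing; the error is in the text of section 2.1.

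**The case against.** The strongest case on the other side is that little is at stake. Worsening is visible elsewhere at the same times: NRS can rise, and adverse events are recorded with severity and summarised by group. The hydrodissection study cited in section 2.6.1 reported an immediate fall of more than 4 points, roughly 40% or more if the scale has 10 points (assumed). At such means the attenuation is small. Flooring also reduces the SD. With a true difference of 0.56 SD, means of 10–60 in the lower group and equal SDs of 20–40, the standardised difference falls from 0.56 to 0.52 at worst, so the loss of power is slight. All of this stands. It limits the point to a cheap improvement of a secondary outcome.

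A reader might infer more than the documents support:
- **That worsened pain is recorded as zero.** No text says so. It is the natural guess, but a blank is equally possible.
- **That the group difference must shrink.** This follows for a shift with equal spread. With unequal spread the difference can grow or arise from nothing.
- **That the within-group PRPPR test is significant by construction.** That needs a test against a constant baseline. Section 2.6.2 names the immediate and 24–36 h assessments just before the within-group test, so the natural pairing is between those two.
- **That harm from one needle would be hidden.** The NRS and the adverse event records would still show it.

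The objection does not remove the gap in the PRPPR item itself or the contradiction on timing.

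**Conclusion.** The point holds in a limited form. PRPPR cannot record worsening, and the article gives no rule for it. Whenever patients worsen, the group mean is biased upward, and the between-group difference can be distorted in either direction.

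The size is unknown, because the proportion who worsen is not given. The figures of 16–27% at means of 20 versus 30% and 1–13% at means of 40–60% rest on normality, equal SDs of 25–40 points and zero-coding, none of which is in the documents. The primary NRS analysis and the sample size do not change.

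The baseline contradiction in section 2.1 needs no assumption and should simply be corrected.

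**What to change.** Before recruitment starts:

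1. Let the PRPPR item record worsening at both time points, either as negative values or as a worse option with its percentage. Do not set a floor at −100%: a rise from NRS 2 to 5 is an increase of 3/2 = 150%.
2. Report the number of participants who worsened in each group, from PRPPR and also from the NRS already collected. Use a count for the NRS, because the inclusion criteria set no minimum score and percentages are unstable at low baselines.
3. Delete PRPPR from the baseline list in section 2.1, and describe it there as assessed, not reassessed, after the procedure.
4. State in section 2.6.2 that the within-group PRPPR comparison is immediate versus 24–36 h.

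The cost is one changed item on the CRF and in the telephone script, plus text edits. Section 2.1 reports that no one had been recruited at manuscript submission. The downside is slightly less comparability with studies that used the 0–100% form.

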### Study registration

2.2

This study was registered with the Clinical Research Information Service (CRIS), Republic of Korea (KCT0011603; 11 February 2026).

### Participants

2.3

The study will include adult participants diagnosed with acute LBP. Before enrollment, all potential participants will receive a comprehensive explanation of the study’s purpose, procedures, expected risks and benefits, data protection policies, and their rights and safety as research subjects. Voluntary participation will be confirmed through written informed consent obtained prior to any study-related procedures.

To ensure a clearly defined cohort and minimize variability in treatment response, only individuals experiencing symptoms for 7 days or less will be included, thereby limiting the sample to participants in the acute phase of LBP.

LBP is commonly classified based on symptom duration as acute (0–6 weeks), subacute (6–12 weeks), and chronic (more than 12 weeks) (3). Similarly, the U. S. National Institutes of Health (NIH) Task Force defines chronicity using a 3-month threshold (11). However, these broad temporal classifications (e.g., 6 or 12 weeks) may introduce substantial heterogeneity within clinical research populations, limiting the ability to accurately assess treatment effects.

Previous studies indicate that most improvements in pain and functional recovery among patients with acute LBP occur within the first 4 to 6 weeks after onset, followed by a markedly slower rate of natural recovery thereafter (3, 12, 13). This recovery trajectory suggests that patients within the first 1 to 2 weeks of symptom onset may represent a distinct clinical subgroup compared to those at 4 to 6 weeks, particularly regarding biological state and likelihood of spontaneous resolution. Moreover, beyond the early phase, greater variability in pain trajectory and prognosis has been reported, further complicating the evaluation of treatment effects. Accordingly, restricting enrollment to patients within the first 7 days of symptom onset may enhance sample homogeneity and improve the validity of early-phase intervention assessments.

Accordingly, the present study adopted a more stringent inclusion window, limiting participant eligibility to within 7 days of symptom onset (0–7 days) rather than the broader conventional acute definition of 0–6 weeks. This refinement aimed to ensure greater cohort homogeneity, minimize potential confounding from spontaneous recovery, and enable a more accurate evaluation of the therapeutic impact of early, targeted intervention in acute LBP.

#### Setting

2.3.1

This multicenter study will take place across four Korean medicine clinics that provide primary outpatient care for musculoskeletal conditions. Participant enrollment and all research-related procedures will be conducted in the outpatient setting of each clinic.

The list of four Korean medicine clinics is as follows:

Kangnyung Korean Medicine Clinic (Anyang, Gyeonggi Province, Republic of Korea).Gwanghwamun Kyung Hee Korean Medicine Clinic (Jongno-gu, Seoul Metropolitan City, Republic of Korea).Mullae Majubom Korean Medicine Clinic (Yeongdeungpo-gu, Seoul Metropolitan City, Republic of Korea).Mapo Hongik Korean Medicine Clinic (Mapo-gu, Seoul Metropolitan City, Republic of Korea).

The interventions will be performed exclusively by Korean medicine doctors who have undergone structured training in ultrasound-guided pharmacopuncture and who are active members of the Academy of Korean Medicine Clinical Anatomy, an organization specializing in ultrasound-based clinical anatomy research.

#### Inclusion criteria

2.3.2

Participants will be included if they meet all of the following conditions:

Age between 20 and 64 years.Acute LBP within 7 days of symptom onset, accompanied by lumbar pain and limited ROM.LBP, with or without referred leg pain.No prior treatment for the current episode of LBP (diagnostic imaging alone is permitted).Ability to understand the study procedures and provide written informed consent.Participants treated with ultrasound-guided pharmacopuncture using a long needle (25G × 100 mm) at Mapo Hongik Korean Medicine Clinic or Gwanghwamun KyungHee Korean Medicine Clinic, or using a short needle (26G × 60 mm) at Mullae Majubom Korean Medicine Clinic or Gangnyeong Korean Medicine Clinic.

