**Figure 1 fig1:**
[figure not shown]
Anatomical structure and ultrasound visualization of the quadratus lumborum–psoas–iliocostalis (QPI) interfascial space. **(A)** Cross-sectional anatomi-cal illustration at the lumbar level demonstrating the anatomical relationship among the quadratus lumborum, psoas major, and iliocostalis muscles. The interfascial plane formed by these muscles, referred to as the QPI space (blue dot), and the intended needle trajectory toward the target layer are illustrated. **(B)** Representative ultrasound image with annotated muscle boundaries corresponding to the anatomical structure, showing the iliocostalis, quadratus lumborum, and psoas major muscles and the intervening QPI interfascial space. **(C)** Corresponding unannotated ultrasound image of the same scanning plane, demonstrating the native sonographic appearance of the QPI interfascial space.

Participants who express willingness to join the study will be screened according to the inclusion and exclusion criteria after receiving a full explanation of the study’s purpose and procedures and providing written informed consent. Eligible participants will be allocated to either the Short Needle Group (SNG; 26G × 60 mm) or the Long Needle Group (LNG; 25G × 100 mm). The two needle types used in this study are shown in Figure 2.

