The interfascial plane of the lumbar region can present varying levels of technical difficulty depending on factors such as body habitus (including BMI and muscle thickness), probe–needle alignment, acoustic properties, and anatomical variations. Anatomical and imaging studies indicate that the target layer is typically located at a depth of approximately 4–6 cm or more from the skin surface (32). Given this depth, conventional 50–60 mm needles may provide limited access or an insufficient safety margin in patients with increased soft tissue thickness. In contrast, anesthesia literature shows that 80–100 mm block needles are routinely used for similarly deep interfascial approaches, such as QL or Erector Spinae Plane (ESP) blocks (33–37). However, within Korean medicine clinical practice, systematic validation of long-needle use—particularly regarding safety, reproducibility, and ultrasound visibility—has been limited, resulting in selective or restricted adoption in real-world settings. Accordingly, the design of the present study holds both methodological and clinical relevance by addressing this gap and evaluating the feasibility of long-needle application in ultrasound-guided interfascial pharmacopuncture.

This study has several methodological strengths, including its prospective design, needle-length comparison framework, multicenter real-world data collection, and incorporation of practitioner usability assessments. Notably, the study was designed to collect not only clinical response outcomes but also procedural variables such as needle handling experience, perceived technical difficulty, and confidence in reaching the target plane. This approach enables exploration of the relationship between therapeutic outcomes and procedural experience. Furthermore, conducting the study in a real-world outpatient clinical setting enhances the applicability of the findings, as it reflects variability in patient characteristics, procedural accessibility, and the operator learning curve. These features contribute to the study’s potential value for future clinical implementation and the development of educational frameworks.

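### Inclusion criterion 6 makes eligibility depend on the needle actually used, while other sections say patients are allocated; if needle choice follows depth or body habitus, case mix will differ between the groups

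*Protocol article*

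**What the plan says.** Section 2.3.2, sixth inclusion criterion: "Participants treated with ultrasound-guided pharmacopuncture using a long needle (25G × 100 mm") at two named clinics, or with the 60 mm needle at the other two.

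Section 2.1 describes the grouping in two ways.

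- As allocation: "Eligible participants will be allocated to either the Short Needle Group (SNG; 26G × 60 mm) or the Long Needle Group".
- As extraction: "All four participating clinical sites routinely use both types of needles in daily practice, depending on actual clinical circumstances"; "two sites will be designated to contribute only cases treated with short needles", and the other two only long-needle cases. It adds: "This approach represents a site-level data extraction scheme, rather than a randomized allocation process". The procedures compared are those "performed in routine clinical practice without modification of standard patient care".

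Section 2.4 ties the needle to group allocation, and section 2.6.1 speaks of 60 patients allocated to each group. Sections 2.1 and 2.3.8 have eligibility decided after consent and before the procedure.

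On the link between depth and needle, the Introduction says 60 mm needles may not reliably reach the deep layers. The Discussion puts the target at about 4–6 cm or more and says "conventional 50–60 mm needles may provide limited access or an insufficient safety margin in patients with increased soft tissue thickness".

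**The concern.** A criterion phrased as having been treated with a given needle can be confirmed only once the needle has been used, so it cannot be checked at the point where the article says eligibility is decided. If operators choose the needle case by case and a site contributes only its designated type, a patient given the other needle at that site is left out. That filters patients within each site through an operator's decision, in addition to any difference between sites.

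The filter matters if the decision is related to outcome. Depth and body habitus are plausible drivers on the article's own rationale. The short-needle group would then lean towards shallower targets and the long-needle group towards deeper ones. Deep target achievement is a stated aim in section 2.1, and NRS change is the primary outcome. Patients never contributed cannot be recovered by later analysis.

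**Working it through.** **1. The plan's own figure.** Inputs from section 2.6.1: d = 0.56, alpha 0.05 (two-sided, section 2.6.2), power 80%. The normal approximation gives n = 2(1.960 + 0.842)²/0.56² = 50.06, so 51 per group. The exact two-sample t-test gives 51.03, so 52 per group and 104 in total, as stated. Allowing 10% dropout, 104/0.90 = 115.6, so 116; the target of 120 exceeds this. The sample size is not in question. The point is who enters the comparison.

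**2. The two readings side by side.**

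| | Needle set by site | Cases selected by needle used |
|---|---|---|
| Supported by | Allocation wording in 2.1, 2.4 and 2.6.1; eligibility settled beforehand in 2.1 and 2.3.8 | Criterion 6 in 2.3.2; extraction wording in 2.1; both needles in use at every site |
| Conflicts with | Unmodified standard care in 2.1 | Allocation wording; timing of the eligibility check |
| Patients left out because of the needle | None | Those given the site's other needle |

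Each reading conflicts with some of the text, and sites following different readings would enrol different cohorts.

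**3. Illustration for reach.** Assumptions, not in the documents: depth is normal with SD 0.8 cm; the 60 mm needle reaches depths up to 6.0 cm and the 100 mm needle up to 10 cm; the log-odds of long-needle use rise by 1 to 4 per cm of depth, with even odds at the mean depth. True short-needle reach in all patients is Φ((6.0 − mean)/0.8). Observed reach is the same proportion among those given the short needle.

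| Mean depth | True short-needle reach | Reach among selected cases, slopes 1 to 4 | Depth difference between groups |
|---|---|---|---|
| 5.0 cm | Φ(1.25) = 89.4% | about 96% to 99.9% | 0.7 to 1.4 SD |
| 5.5 cm | Φ(0.625) = 73.4% | 85.2% to 98.0% | 0.7 to 1.4 SD |

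With slope 0 (choice unrelated to depth), observed and true reach agree and the groups do not differ in depth.

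**4. Illustration for NRS.** Section 2.6.1 gives reductions of 2.74 and 1.76, so the implied SD is (2.74 − 1.76)/0.56 = 1.75. With no true needle effect and a case-mix difference b, SE = 1.75 × √(2/n), and the two-sided rejection rate is 1 − Φ(1.96 − b/SE) + Φ(−1.96 − b/SE).

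| b (points) | n = 52 per group | n = 60 per group |
|---|---|---|
| 0.25 | 11% | 12% |
| 0.5 | 31% | 35% |
| 1.0 | 83% | 88% |

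For b = 0.5 and n = 52: SE = 0.343, b/SE = 1.457, rate 0.308. The documents give no basis for the value or sign of b. The table shows only how sensitive a study of this size is to such a difference.

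**The case against.** The strongest reply is that the designation of a clinic fixes the needle there. Sections 2.4 and 2.6.1 read that way. Criterion 6 would then be known in advance and nobody would be left out. This is a fair reading, but it does not fit unmodified care at clinics that use both needles, so the ambiguity stands.

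A reader might go further and infer that short-needle clinics discard their deep-target patients. The article does not say so. It leaves clinical circumstances undefined, and depth-driven choice is only an inference from the Introduction and Discussion.

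A reader might also infer that failed short-needle attempts disappear and that reported reach will be close to 100%. The documents do not support this either. No section describes switching needles after failure. A patient punctured with the short needle without reaching the plane has still been treated with it. Section 2.1 records insertions and tip arrival, section 2.6.2 summarises the reach success rate, and failed access is not listed as a dropout reason in section 2.3.4.

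It is also true that section 2.6.2 treats reach as a supportive variable that does not directly bear on the primary interpretation, that the Discussion concedes selection bias from site-based allocation, and that section 2.6.2 allows ANCOVA or regression. These help only in part. The concession does not name selection on the needle used, adjustment is triggered only by significant baseline differences, and target depth is not among the listed baseline variables, although height and weight are.

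**Conclusion.** The point holds as an unresolved contradiction with a conditional bias. Criterion 6 and the extraction wording select on the needle used; the allocation wording and the timing of the eligibility check say otherwise; the existing limitation statement and conditional adjustment do not settle it.

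If needle choice follows depth or body habitus, the groups will differ in case mix and short-needle reach will tend to be overstated. The NRS comparison could be biased, but neither direction nor size can be fixed from the documents. If choice is unrelated to depth, or if the site sets the needle for every eligible patient, this selection bias does not arise. All magnitudes above depend on assumed depth distributions, needle reach, selection strengths or NRS differences and are illustrations only. The correction belongs before enrolment, and section 2.1 states that nobody had been recruited at submission.

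**What to change.** 1. Reconcile sections 2.1, 2.3.2, 2.4 and 2.6.1 on whether the needle is set by site or cases are selected by the needle used, and use one term throughout.
2. In criterion 6, replace the treated-with condition by one known before puncture: the intended needle, written on the CRF beforehand. Define the group by it.
3. Keep every such patient in that group for all outcomes, including failed access or a change of needle. Record reach as whether the intended needle reached the plane, so that success with another needle is neither credited to nor confused with the intended one.
4. Log all otherwise eligible patients at each site with the needle used and the reason. If needles remain the operator's choice, recording intent does not remove selection, and this log is what makes it visible.
5. Pre-specify BMI (height and weight are already collected) and skin-to-target depth, read from the stored ultrasound images, as covariates in the primary NRS model, whatever the baseline tests show.

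The cost is a few CRF fields, a screening log and some image reading, with no extra patient procedure. If needles are changed, the contrast is diluted. As an assumed range, crossover of 10% to 40% in one group, with patients who change responding as in the other group, shrinks d from 0.56 to 0.56 × 0.90 = 0.50 or 0.56 × 0.60 = 0.34. Power at 60 per group, Φ(d√30 − 1.96), then falls from 87% to 79% or 45%. Confounding by site remains and should stay a stated limitation.
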